## 2. Methods and timing for assessing recording and analyzing efficacy parameters

Blood samples will be taken for serological assays at days 0, 3, 7, 14 and 21 after 1st and 2nd doses of vaccine. This study is an open study but all sera will be coded and blinded assays will be conducted by National Institute of Biological Standards and Control, Health Protection Agency and Istituto Superiore di Sanità, (SRH, HI, and neutralisation assays) on samples collected up to 21  $\pm$  4 days after second dose of vaccine. These assays will be run with the international human anti-H5N1 standard plasma pool to allow comparison with other H5N1 pandemic clinical trials. When these serological assays are completed the code will be broken and the results sorted into appropriate vaccine group. The influence of the use of adjuvant and different antigen strengths on the immunogenicity of a viral A/H5N1 influenza vaccine on each of the sampling days and particularly 21 days post vaccination will then be assessed according to the three evaluation criteria defined by the CHMP. For each vaccine group the following will be calculated:

- The number of subjects who seroconvert or show significant increases in anti-haemagglutinin antibody titre;

- The mean geometric increase;

- The proportion of subjects achieving an HI titre  $\geq 40$  or SRH  $> 25 \text{ mm}^2$ .

The immunogenicity of the vaccine will also be evaluated by

- Producing a detailed time course of the immune response to vaccination including the kinetics of the T, B- and serum antibody responses
- The ability of the vaccine to induce long lasting immunity using the blood samples collected at 6 and 12 months after vaccination.
- The ability of the vaccine to induce cross-reactive immunity to other H5 strains.
- Examining the quality and repertoire of the antibody response.

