#### European Union (EU) requirements for influenza vaccines

The Committee for Medicinal Products for Human Use (CHMP) has defined a set of regulatory criteria influenza vaccines need to meet in order to obtain a marketing license in the European Economic Area [30]. The vaccine efficacy is tested by the haemagglutination inhibition (HI) [31], or single radial haemolysis (SRH) assays [32]. An HI titre  $\geq 40$  (or an equivalent SRH  $> 25\text{mm}^2$ ) indicates 50% protective levels of serum antibody against influenza infection in man. The EU requirements for harmonisation of influenza vaccines require annual clinical trials for licensing. The vaccine should fulfil one of the following evaluation criteria for each strain in adults aged 18-60:

1. The number of seroconversions or significant increases in anti-haemagglutinin antibody titre should be  $> 40\%$ ;

2. Mean geometric increase >2.5;

3. The proportion of subjects achieving an HI titre  $\geq 40$  or SRH > 25mm^2 should be >70%.

There are no requirements for inactivated vaccines to evoke a cellular immune response. The World Health Organisation (WHO) has prepared a number of recommendations for increased preparedness and research [33]. The CHMP require pandemic vaccine to meet all the current evaluation criteria for marketing authorisation. They also recommend measuring neutralising antibodies, and suggest more detailed analysis of the immune response for example detection of antibodies directed against neuraminidase and cell mediated responses [34].

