#### PANFLUVAC consortium

The WHO commissioned H5N1 seed virus NIBRG-14 virus, which is derived from the genetically modified A/Vietnam/1194/2004 (H5N1) virus will be used in this study. Plasmids for the H5 HA and N1 NA were cloned from A/Vietnam/1194/2004 (H5N1). These were used with the six PR8 backbone plasmids and four PR8 polymerase expression plasmids to generate a candidate H5N1 vaccine reference strain using the reverse genetics procedures. The cloned H5 HA was engineered to remove the polybasic amino acids at the cleavage site (a molecular correlate of pathogenicity in birds and mice). This rescued virus - NIBRG-14 - was tested for lack of pathogenicity in chickens and ferrets, before removal from the Biological Safety Level (BSL) 4 containment and being assigned a BSL2+ status.

Berna Biotech Ltd. has produced an H5N1 virosomal influenza vaccine. The NIBRG-14 virus was propagated in the allantoic cavity of embryonated hens' eggs. The virus was inactivated by beta-propiolactone and HA and phospholipids were solubilised with the detergent octaethyleneglycol

- Provide a detailed time course of the immune response to vaccination with a novel influenza subtype including the kinetics of the T-cell, B-cell and antibody responses
- Examine the effect of the use of adjuvant and different antigen strengths to provide a dose sparing approach
- 1) Evaluation of the local and systemic safety and tolerability of parenterally administered virosomal H5N1 influenza vaccine, with and without 3rd generation ISCOM™ adjuvant.
- 2) To evaluate the immunogenicity of a virosomal H5N1 influenza vaccine including:

The objectives and purpose of this trial are:

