1. **Specification of efficacy parameters**

In the absence of true efficacy markers like prevention of illness and/or reduction of morbidity and mortality, serum anti-HA antibodies are the most commonly measured correlate of protection against influenza [57] or surrogates of efficacy. The CHMP have defined criteria for the annual update for seasonal influenza vaccines, which measure the serological responses by the haemagglutination inhibition or single radial haemolysis assays. An HI titre  $\geq 40$  (or an equivalent SRH  $> 25\text{mm}^2$ ) indicates 50% protective levels of serum antibody against influenza infection in man. The EU evaluation criteria in groups of at least 50 adults aged 18-60 approximately at 3 weeks after vaccination are:

  - The number of seroconversions or significant increases in anti-haemagglutinin antibody titre should be  $> 40\%$ ;
  - Mean geometric increase  $> 2.5$ ;

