## 8 Assessment of Efficacy

4. **Procedures for monitoring subject compliance**

This study is a vaccine study and the daily log of events and CRF will be used to record if subjects have been vaccinated and provided the appropriate trial samples.

3. **Medication permitted (including rescue medication) and not permitted before and /or during trial**

All subjects enrolled in this trial may continue their normal medication throughout the study. Subjects may continue to take therapy for chronic medical conditions, but must be maintained on a stable regimen for at least 2 weeks prior to study entry as assessed by their Medical History. However, subjects taking medication for malignant diseases or medication which may cause immunosuppression, will be excluded from enrolling in this study.

If anaphylactic shock occurs after vaccination, it will be treated according to the standard routines at Haukeland University Hospital using hydrocortisone sodium succinate (Solu-Cortef 100mg), dexchlorfeniramine (5mg/mL), atropine (1mg/mL), adrenaline (1mg/mL and 0.1mg/mL). Use of other medication including over-the-counter products will be discouraged during the study. Investigational drugs are prohibited during the course of the study.

- The proportion of subjects achieving an HI titre  $\geq 40$  or SRH  $> 25\text{mm}^2$  should be  $> 70\%$

The CHMP require for marketing authorisation of a pandemic vaccine that the vaccine fulfils all current evaluation criteria despite the immunological naivety of the host. The serological responses of the four vaccine groups will be evaluated and the ability of each group to meet the CHMP criteria will be determined. The ability of the different vaccine strengths to elicit neutralising antibodies will also be investigated.

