**2. The number of subjects planned to be enrolled and reason for choice of sample size**

Sixty young healthy subjects (aged 19-50 years old) will be randomly assigned to one of four groups, each group will contain 15 subjects and the investigators will aim to have an equal distribution of males and females in each group and similar age distribution.

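### Section 8.2 assigns the adjuvant and dose-sparing question to CHMP criteria computed separately in each group of 15, and defines no between-group estimate or interval

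*Protocol*

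**What the plan says.** The trial objectives, printed just before the heading of section 4, include this one: "Examine the effect of the use of adjuvant and different antigen strengths to provide a dose sparing approach". Section 8.2 says how it will be met. "The influence of the use of adjuvant and different antigen strengths on the immunogenicity" on each sampling day, and particularly 21 days post vaccination, "will then be assessed according to the three evaluation criteria defined by the CHMP". It continues: "For each vaccine group the following will be calculated", and lists the number who seroconvert or show a significant titre increase, the mean geometric increase, and the proportion reaching HI 40 or SRH above 25 mm².

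Section 8.1 gives the cut-offs (above 40%, above 2.5 and above 70%), says that they apply to groups of at least 50 adults, and states that "the ability of each group to meet the CHMP criteria will be determined". Section 10.2 fixes the size: "each group will contain 15 subjects".

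The paragraph on protocol deviations at the end of section 8 mentions comparative serological analyses, but only to decide whether off-schedule subjects are included. It defines no comparison.

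**The concern.** The question is about differences between groups, and the method named for it looks at one group at a time. That Group 4 meets a criterion and Group 1 does not is no estimate of what the adjuvant adds: the two may differ by one subject, or by many. The reverse also holds, since two groups can both meet a criterion while one responds clearly better.

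At stake are the adjuvant and dose-sparing conclusions. Chance crossings of a threshold could suggest an effect or hide one. The criteria are also applied to groups less than a third of the size for which the protocol quotes them (15 against at least 50).

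**Working it through.** The protocol states no power, error rate or expected response, so there is no figure of its own to reproduce. The check asks how often two groups with the same true response would be classified differently.

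**Inputs.** Group size is 15 (section 10.2). The cut-offs come from section 8.1 and the background section on EU requirements. The true response rates are not in the protocol and are assumed over a range.

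**Seroprotection, above 70%.** 0.70 × 15 = 10.5, so at least 11 of 15 are needed. With true rate p, let q = P(X ≥ 11) for X binomial (15, p). Two independent groups with the same p get opposite verdicts with probability 2q(1 − q).

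| True rate p | q | 2q(1 − q) |
|---|---|---|
| 0.50 | 0.059 | 11% |
| 0.60 | 0.217 | 34% |
| 0.65 | 0.352 | 46% |
| 0.70 | 0.515 | 50% |
| 0.75 | 0.686 | 43% |
| 0.80 | 0.836 | 27% |
| 0.85 | 0.938 | 12% |
| 0.90 | 0.987 | 2.5% |

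**What group size changes.** At n = 50, more than 70% means at least 36. The same formula gives 10% at p = 0.60 (q = 0.054) and 11% at p = 0.80 (q = 0.939), against 34% and 27% at n = 15. Near the threshold little changes: at p = 0.70 it is 49% (q = 0.447).

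**Seroconversion, above 40%.** 6/15 is exactly 40%, so at least 7 are needed. Opposite verdicts occur 23% of the time at a true rate of 0.30, 48% at 0.40, 42% at 0.50, 17% at 0.60 and 3% at 0.70.

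**Geometric mean increase, "Mean geometric increase >2.5".** By a normal approximation, two groups with a true 2.5-fold rise get opposite verdicts half the time. Assuming an SD of 0.4 to 0.7 log10, the figure is 29 to 42% at a true 2-fold rise and 5 to 23% at a true 4-fold rise.

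**What an opposite verdict can look like.** 11/15 meets the 70% criterion and 10/15 does not. The difference is 6.7 percentage points, with a Wald 95% interval of about −26 to +39 points.

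**The reverse error.** With true rates of 0.75 and 0.95, q is 0.686 and 0.999. The chance of the same verdict is 0.686 × 0.999 + 0.314 × 0.001 = 0.69, so a real 20-point difference would go unseen 69% of the time on this criterion.

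**Precision of a direct comparison.** For an unadjusted ratio of geometric mean titres with 15 per group, the 95% limits lie a factor of 10^(2.048 × SD × √(2/15)) either side of the estimate. With an assumed SD of 0.4, 0.5 or 0.6 log10 that factor is 2.0, 2.4 or 2.8.

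**The case against.** The strongest reply is that section 8.2 lists three quantities without cut-offs, while the meets-or-not statement is a separate sentence in section 8.1. Nothing says outright that the adjuvant effect will be concluded from one group passing and another failing. The deviations paragraph also expects some comparative analysis, and an analysis plan that is not shown may define it. This stands in part: a reader might infer that the protocol rules out a direct comparison, and it does not. But section 8.2 goes beyond leaving the method open. It names the comparative question and ties it to the CHMP criteria, so an analysis plan would have to supplement or depart from that sentence.

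A reader might also infer that the stated method has far less power than a comparison of titres, or that cutting at 40 discards most of the information. The documents do not support either claim. The protocol names no test, so there is no stated power to compare, and one of its three measures, the mean geometric increase, already uses uncut titres on the log scale.

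Nor should the 50% be read as a product of groups of 15. It is the maximum of 2q(1 − q) at any group size.

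Finally, immunogenicity is a secondary endpoint of a phase I pilot, and section 10.1 says that a larger study with higher power would be needed. That limits the consequences, but dose sparing is still a stated objective.

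**Conclusion.** The point holds in a limited form and should be corrected. The only method that the protocol fixes for the adjuvant and dose-sparing question is a set of per-group CHMP results, with no between-group estimate or interval. If these are read as meets or does not meet, equally immunogenic groups of 15 get opposite seroprotection verdicts more than a quarter of the time for true rates from about 0.57 to 0.80, peaking at 50% near 0.70. Far from the threshold the risk is small. These figures assume independent groups with equal true rates. The true rates are unknown, so the actual risk could lie anywhere in the table.

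The design supports direct contrasts, with two limits. Groups 4 and 1 share 30 µg HA and differ in adjuvant. Groups 2 to 4 share 50 µg adjuvant, and a reader might take them to differ only in HA. They do not: Table 1.1 and the product tables show lecithin rising with HA (3.9, 19.5 and 78.0 µg). Groups 2 and 3 differ from Group 1 in adjuvant and antigen together, so that contrast cannot separate the two.

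**What to change.** In section 8.2, replace the sentence that assigns the comparative question to the CHMP criteria with the following:

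- The adjuvant effect is estimated by the Group 4 to Group 1 ratio of geometric mean titres.
- The antigen-strength effect is estimated by the trend in log titre over log HA dose in Groups 2 to 4, described as a formulation-dose trend because lecithin rises with HA.
- Groups 2 and 3 against Group 1 are reported as descriptive ratios of the adjuvanted lower-dose formulations to the unadjuvanted 30 µg formulation.
- Each is taken 21 days after the second dose, on log titres adjusted for the day 0 titre, with a 95% confidence interval. Equivalence is not claimed from a non-significant difference.
- The three CHMP measures are kept as per-group description.

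The cost is one paragraph and one extra regression on sera already planned; no new visits, samples or subjects are needed. The drawback is wide intervals at 15 per group, which show openly how little a trial of this size can settle.

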#### Deviation from protocol

The investigators will adhere and try to avoid deviations from the protocol. The clinical investigators will document and explain any deviations from the approved protocol. Blood sampling for kinetic studies (T, B and antibody) can be collected within the following time frames after both the first and second doses of vaccine –  $14 \pm 12$  days (pre-screening) and after the first vaccination; day  $0 \pm 0$ ,  $3 \pm 1$ ,  $7 \pm 2$ ,  $14 \pm 2$ ,  $21 \pm 4$ . Subjects who do not adhere to these sampling time points have deviated from the protocol and their inclusion in the comparative serological analyses will be evaluated by the investigators.

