| Vaccination Day 21    | ±4                               |                  | ✓                                           |                             | ✓                              | ✓                       |                          |                        | ✓                               | ✓                                  |               |             |                                 |                                       | ✓                            | ✓                      |
| Day 24                | ±1                               |                  |                                             |                             |                                | ✓                       |                          |                        | ✓                               | ✓                                  |               |             |                                 |                                       | ✓                            | ✓                      |
| Day 28                | ±2                               |                  |                                             |                             |                                |                         |                          |                        | ✓                               | ✓                                  |               |             |                                 |                                       | ✓                            | ✓                      |
| Day 35                | ±2                               |                  |                                             |                             |                                |                         |                          |                        | ✓                               | ✓                                  |               |             |                                 |                                       | ✓                            | ✓                      |
| Day 42                | ±4                               |                  |                                             |                             |                                |                         |                          |                        | ✓                               | ✓                                  |               |             |                                 |                                       | ✓                            | ✓                      |

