#### Fifth visit: Day 14 ( $\pm 2$ days) post 1st vaccination

- **Biochemical parameters:** CRP, transaminases (ASAT, ALAT), alkaline phosphatase, Gamma GT, total bilirubin
- **Immunology tests:** ANA antibodies

Seventh visit: Day 3 ( $\pm 1$  day) post 2nd vaccination

- The local and systemic reactions, occurrence of adverse events, and use of analgesic or antipyretic medications will be assessed. Data collection will be recorded in the CRF.
- The results of the screening samples will be reviewed.
- Screening and trial blood samples will be collected by venipuncture. Trial blood and Orasure samples will be collected to measure the antibody, T- and B-cellular and local antibody responses, respectively.
- The adverse event form will be reviewed.
- Schedule the next clinic visit.

The following haematological and biochemical screening tests will be carried out:

- **Haematology:** red blood cell count, white blood cell count, % of neutrophils, eosinophils, basophils, monocytes, lymphocytes, platelets
- **Biochemical parameters:** CRP

Eight visit: Day 7 ( $\pm 2$  day) post 2nd vaccination

- The results of the screening samples will be reviewed.
- The adverse event form will be reviewed.
- Trial blood and Orasure samples will be collected to measure the antibody, T- and B-cellular and local antibody responses, respectively.
- Schedule the next clinic visit.

Ninth visit: Day 14 ( $\pm 2$  days) post 2nd vaccination

- The adverse event form will be reviewed.
- Trial blood and Orasure samples will be collected to measure the antibody, T- and B-cellular and local antibody responses, respectively.
- Schedule the next clinic visit.

The trial blood samples will be collected at 0, 3, 7, 14 and 21 days after each dose of vaccine (as detailed below) and at 6-12 months post vaccination to be used in serological assays and to study the kinetics of the T- and B-cellular responses. The serological assays (HI, SRH and neutralisation assays) will be carried out at the reference laboratories the National Institute of Biological Standards and Control and Health Protection Agency, UK and Istituto Superiore di Sanità, Italy according to established standard operating procedures (SOP). The modified HI assay using horse erythrocytes will be used as it shows increase sensitivity over the conventional HI test for detection of H5N1 antibody [56]. The kinetics of the immune response elicited after vaccination

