| Feber >38°C i løpet av siste 72 timer                                      |     |    |
| Akutt luftveis sykdom siste 7 dager                                        |     |    |
| Kvinne: gravid eller ammende                                               |     |    |
| Sykdom som kan påvirke evnen til å gjennomføre deltagelse i studien        |     |    |
| Fått blodprodukter eller immunoglobulin parenteralt siste 3 måneder        |     |    |
| Kjent eller mistenkt immunsviktssykdom                                     |     |    |
| Bruk av medisiner som svekker immunforsvaret                               |     |    |
| Bruk av immunstimulerende medikamenter                                     |     |    |
| Vaksinert i en 4 ukers periode før første vaksinasjon                      |     |    |
| Vært med på andre kliniske utprøvinger siste måneden                       |     |    |

Delager ID # \_\_\_\_\_ Kjønn \_\_\_\_\_ Alder \_\_\_\_\_ Initialer \_\_\_\_\_

Åpne rubrikker skal merkes av med aktuell dato for hvert besøk. Grå rubrikker skal ikke fylles ut.

| Dato                             | Kontrollert
egenmeldingsskjema
for bivirkninger | Tatt hematologiske
prøver | Tatt biokjemiske
prøver | Tatt immunologiske
prøver | Tatt spyttprøve | Tatt blod til studien |
|----------------------------------|-------------------------------------------------------|------------------------------|----------------------------|------------------------------|-----------------|-----------------------|
| for undersøkelse
Dag -14 ± 12 |                                                       |                              |                            |                              |                 |                       |
| Vaksinasjon
Dag 0             |                                                       |                              |                            |                              |                 |                       |
| Dag 3 ± 1                        |                                                       |                              |                            |                              |                 |                       |
| Dag 7 ±                          |                                                       |                              |                            |                              |                 |                       |

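### Table 5.1 and the case report form time the post-dose-2 samples from Day 0, the visit lists and section 8.2 time them from dose 2, and the deviation rule does not settle which governs

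*Protocol*

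**What the plan says.** - **Dose 2.** Table 5.1 lists it as "Vaccination Day 21 | ±4", so it may be given on study days 17 to 25.
- **Table 5.1, later rows.** On the same scale, the following visits are Day 24 ± 1, Day 28 ± 2, Day 35 ± 2 and Day 42 ± 4.
- **Case report form visit log (Appendix).** The same day labels appear, but Day 28 carries ± 1. The form also tells staff to enter the actual date of each visit: "Åpne rubrikker skal merkes av med aktuell dato for hvert besøk".
- **Visit lists (section 5, Study procedure).** The first post-boost visit is headed "Seventh visit: Day 3", ± 1 day, after the second vaccination. Visits eight to ten are 7 ± 2, 14 ± 2 and 21 ± 4 days after it.
- **Section 8.2.** "Blood samples will be taken for serological assays at days 0, 3, 7, 14 and 21 after 1 st and 2 nd doses of vaccine". Immunogenicity "on each of the sampling days and particularly 21 days post vaccination will then be assessed" against the CHMP criteria.
- **Section 8, Deviation from protocol.** "Blood sampling for kinetic studies (T, B and antibody) can be collected within the following time frames after both the first and second doses". The windows listed next (0 ± 0, 3 ± 1, 7 ± 2, 14 ± 2, 21 ± 4) are nevertheless introduced as following the first vaccination. Then: "Subjects who do not adhere to these sampling time points have deviated from the protocol". Whether such subjects stay in the comparative serology is for the investigators to evaluate.
- **Section 10, the matching paragraph on deviations and missing data.** It repeats the rule for all blood samples, but with 7 ± 1.

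**The concern.** A schedule counted from Day 0 and a schedule counted from dose 2 give different dates whenever dose 2 is off day 21, which the protocol allows by up to four days either way. No section says which one governs. The same sample can therefore be on time under one schedule and a deviation under the other, and the rule meant to define a deviation is itself unclear about its starting point.

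The time course of the response is a stated objective, and the CHMP criteria are read at 21 days in particular. The protocol's own background section says that serum antibody rises from 2 to 6 days after vaccination in primed subjects and that antibody-secreting cells appear at about day 7. If that carries over to a second H5N1 dose (an assumption), the first two post-boost samples fall where a few days change the reading.

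Inclusion of off-window subjects is left to judgement with no criterion. The study is open, and sections 5 and 5.6 say that the investigators know the sample code. An inclusion decision made case by case is then open to influence from the vaccine group.

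**Working it through.** **Inputs.** Dose-2 day *d* = 17 to 25 (Table 5.1). Study-day windows come from Table 5.1 and the form's log. Dose-anchored windows come from the visit lists.

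**1. Reproduce the table.** 21 + 3, 7, 14 and 21 = 24, 28, 35 and 42. Table 5.1's windows (± 1, ± 2, ± 2, ± 4) equal those in the visit lists. So with dose 2 on day 21, Table 5.1 and the visit lists are the same schedule.

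**2. Real days since dose 2 if the study-day windows are applied literally.** Earliest = (label − window) − 25. Latest = (label + window) − 17.

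| Visit label | Study days | Days since dose 2 | Dose-anchored window | Furthest from nominal |
|---|---|---|---|---|
| Day 24 ± 1 | 23–25 | −2 to 8 | 2–4 | 5 (nominal 3) |
| Day 28 ± 2 (Table 5.1) | 26–30 | 1 to 13 | 5–9 | 6 (nominal 7) |
| Day 28 ± 1 (form) | 27–29 | 2 to 12 | 5–9 | 5 (nominal 7) |
| Day 35 ± 2 | 33–37 | 8 to 20 | 12–16 | 6 (nominal 14) |
| Day 42 ± 4 | 38–46 | 13 to 29 | 17–25 | 8 (nominal 21) |

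In every row the furthest distance is that row's own visit window plus 4 days, and the 4 days are the dose-2 tolerance. For example, 5 = 1 + 4 and 8 = 4 + 4. The anchor conflict therefore contributes at most 4 days; the rest is ordinary visit tolerance.

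**3. Can one date satisfy both schedules?** The first post-boost visit must fall on days *d* + 2 to *d* + 4 and also on days 23 to 25. That needs *d* + 4 ≥ 23 and *d* + 2 ≤ 25, so *d* = 19 to 23. For *d* = 17, 18, 24 or 25, which is 4 of the 9 permitted days, no date works. With *d* = 17, for instance, one schedule gives days 19–21 and the other days 23–25.

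For the form's Day 28 ± 1, *d* + 9 ≥ 27 and *d* + 5 ≤ 29 give *d* = 18 to 24, so no date works for *d* = 17 or 25. Table 5.1's Day 28 ± 2, Day 35 and Day 42 overlap the dose-anchored windows for every permitted *d*.

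**4. After anchoring on dose 2.** All samples lie 2–4, 5–9, 12–16 or 17–25 days after the boost. In study days that is 19–29, 22–34, 29–41 and 34–50, wider than the 23–25, 26–30, 33–37 and 38–46 that Table 5.1 prints.

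**5. Day-7 window.** It is ± 2 in Table 5.1, the visit lists and section 8. It is ± 1 in section 10 and, for Day 28, on the form.

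**The case against.** The best reply is that the operative text already uses one anchor. Section 8.2 counts sampling days after each dose, the visits are headed by dose, and both deviation paragraphs open by referring to both doses. Table 5.1 is titled a summary, and its later rows are exactly 21 plus the dose-anchored days, so it reads naturally as the nominal version of the same schedule. Each visit ends by booking the next, which suggests that staff would count from the dose actually given. Visit and vaccination dates are recorded, so true intervals can be recovered. The time variable for a kinetics analysis is commonly left to the analysis plan.

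Most of this stands, and it limits the point to a risk. What it does not remove is that neither the table nor the form says its later rows move with dose 2, while each prints separate windows for them. The deviation rule contradicts itself on the starting point. Recorded dates identify an off-time sample but cannot move it.

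Three stronger readings are tempting, and the documents do not support them.

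- **Samples taken before the boost.** The −2 above is a formal limit. It arises only at Day 24 with dose 2 on day 24 or 25, and it would contradict the visit order and the heading of the seventh visit.
- **A share of samples expected off-window.** Any percentage needs visits to be booked independently of the dose-2 date, for which nothing in the protocol speaks.
- **A timing shift that mimics a dose or adjuvant effect across a whole group.** Section 5.3 staggers each group as 5 and then 10 subjects after a week's observation, so one shifted week would not move a whole group.

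**Conclusion.** The inconsistency holds: two anchors, full agreement only for dose 2 on day 21, and no compatible date for the first post-boost visit on 4 of the 9 permitted dose-2 days. The possible displacement from the nominal post-boost day is 5 to 8 days at worst, of which the anchor accounts for at most 4. Those figures rest on Table 5.1 or the form being applied literally from Day 0 with dose 2 at an end of its window. Since section 8.2 and the visit lists count from the dose, that is a possibility to close off, not a forecast of how the trial will run.

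The deviation rule is the second part of the point. Its starting point is ambiguous, its day-7 window differs between sections 8 and 10, and it leaves inclusion to code-aware investigators without a criterion. The change is worth making because it costs almost nothing and has to be in place before blood is drawn.

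**What to change.** 1. Reconcile Table 5.1, the form's visit log and the deviation paragraphs in sections 8 and 10 so that every post-dose-2 sampling window is counted from one anchor, the recorded date of the last dose. In the table and form, relabel four rows or add a footnote. In the two paragraphs, remove the wording that ties the list to the first vaccination.
2. Reconcile the day-7 window, so that one tolerance appears in Table 5.1, the visit lists, section 8, section 10 and the form's Day 28 row.
3. State that kinetics are analysed by actual days since the last dose.
4. For tables by nominal day, replace the investigators' evaluation with a fixed rule: a sample enters if its actual day lies in the stated window, whatever the vaccine group.

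The cost is edits to four rows in two places, two paragraphs and two analysis sentences. Visit and vaccination dates are already on the form, and no extra visits or samples are needed. None of this bears on when dose 2 is given.
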